## Abstract

**Introduction:**

Poor access to surgical wound swabbing in the community often results in delayed or inappropriate antibiotic prescribing for surgical site infections. This delay can contribute to prolonged wound healing and poor antimicrobial stewardship. Patient self-swabbing at home could improve access to diagnostic testing, but its feasibility and acceptability remain unexplored.

**Methods and analysis:**

TREASURE is a multicentre, mixed-methods feasibility study. A total of 40 patient participants and 10 staff stakeholders will be included. 40 adult patients undergoing cardiac surgery via median sternotomy will be recruited from Harefield Hospital (n=25) and the Royal Sussex County Hospital (n=15). Eligible participants will receive a coproduced self-swabbing set of instructions and kit at discharge and perform wound swabbing at home within 1–21 days, observed remotely by a researcher via Microsoft Teams. Swabs will be couriered to a central laboratory for bacterial culture with antimicrobial susceptibility testing for pathogens.

The primary feasibility outcome is the proportion of patients successfully completing self-swabbing at home to obtain usable culture swabs with samples received at the laboratory within 24 hours and deemed suitable for processing. Secondary safety and acceptability outcomes include usability of the kit and instructions; patient satisfaction; viability of samples for laboratory analysis; and recruitment and retention rates. A 30-day follow-up will capture wound complications, antibiotic prescribing and healthcare utilisation via patient questionnaires, case note review, general practitioner confirmation and patient interviews. 10 staff stakeholders will be interviewed to inform pathway development.

Quantitative data will be analysed descriptively, with proportions reported alongside 95% CIs. Qualitative data from patients will undergo thematic analysis, and stakeholder interviews will be coded using Normalisation Process Theory. An early health economic model will be developed to explore resource use, costs and proportions of appropriate and timely antibiotic use between current pathways and a proposed pathway, including self-swabbing.

**Ethics and dissemination:**

West of Scotland Research Ethics Service has reviewed and approved the study (REC reference: 25/WS/0079). Findings will be disseminated through the study website, a webinar, peer-reviewed publications, conference presentations, patient and public involvement-led activities and engagement with National Health Service (NHS) stakeholders.

**Trial registration numbers:**

NCT07200401, ISRCTN28466609.

STRENGTHS AND LIMITATIONS OF THIS STUDYThe study uses a mixed-methods feasibility design incorporating quantitative process measures and qualitative interviews to assess the practicality of the intervention.Patient and public involvement was integrated into the development of study materials, including the swab kit design and instructions, to ensure methodological appropriateness.Multiple data outcomes (recruitment, adherence, acceptability and laboratory processing metrics) will be collected to evaluate key feasibility parameters needed for a future trial.Conducting the study within a single surgical specialty and across two hospital sites may limit generalisability.

## Introduction

 Surgical wound complications remain a significant clinical and public health challenge, affecting patient recovery, healthcare costs and antimicrobial resistance (AMR). Poor access to wound swabbing in the community frequently results in patients receiving delayed or inappropriate antibiotic treatment for surgical site infections (SSIs).^1 2^ Such delays can exacerbate complications, prolong healing and contribute to the global threat of AMR. While patient self-swabbing at home offers a practical means of improving diagnostic access, its feasibility and effectiveness have not yet been explored.

Most SSIs develop after patients have been discharged from hospital, with the majority being classed as superficial infections.^3 4^ In the UK, current standard practice at discharge is to advise patients to contact their general practitioner (GP) if wound concerns arise. Increasingly, patients are also monitored remotely via telephone calls, text messages, emails or virtual consultations.^5^ However, when infection is suspected, patients may be required to attend either their GP surgery or hospital for wound review and, if deemed appropriate, specimen collection (swabbing).

Swab cultures can aid the identification of significant organisms and guide the choice of antibiotic, supporting a move away from empiric broad-spectrum prescribing towards narrower, targeted therapy.^6^ This serves to increase the likelihood of effective treatment and reduce unnecessary broad-spectrum antibiotic exposure, which in turn mitigates the development of AMR. While wound swabbing is not required in every case and clinical assessment remains central, timely access to culture results provides clinicians with valuable information to optimise care and stewardship.^7^

Several barriers restrict timely access to wound swabbing. These include: difficulty obtaining GP appointments^8^ and the inconvenience of hospital visits, which may involve additional costs, travel, carer support and time away from work. These challenges raise important questions: how can wound infections be identified earlier; could point-of-care testing in primary care improve outcomes and reduce unnecessary antibiotic use; and what role could patient self-care and carer involvement play in infection management?^9^

The scale of the problem is considerable. Data from 21 patients across six cardiothoracic centres indicate that only 2% of patients reporting wound problems following cardiac surgery underwent swabbing, while only 28% of those prescribed antibiotics for wound complications had a swab taken.^10^ Of the approximately five million surgical procedures performed annually in England, an estimated one million patients (20%) develop a wound complication, with around 250 000 (5%) experiencing a wound infection.^11^ These complications can require additional surgery, may take months or years to resolve, negatively impact quality of life^12^ and contribute to an estimated annual cost to the NHS of £1 billion, with individual cases costing up to £100 000 to manage.^13 14^ The UK Health Security Agency (UKHSA) reported in 2018 that 20% of antibiotics prescribed in primary care were inappropriate.^15^ Inappropriate antibiotic use further compounds the risk of AMR, delays recovery and increases mortality and healthcare expenditure worldwide.^16^

International and national policy and research priorities highlight the importance of addressing this issue. In 2023, the WHO launched a global AMR forum to tackle this threat to planetary health.^17^ In the UK, the Royal College of General Practitioners called for better access to point-of-care testing to support accurate diagnosis and treatment of infections and the James Lind Alliance, which brings together patients, carers and clinicians, identified infection diagnosis and management as a key research priority.^9^ Furthermore, the NHS Long Term Plan emphasises improving service accessibility and supporting safe, convenient care at home,^18^ while commitments to reduce patient travel align with the NHS target of achieving carbon net zero by 2040.^19^

There is an established precedent for self-swabbing. Self-swabbing and testing for Covid were quickly and successfully implemented nationally in the UK.^20^

Against this backdrop, the potential for home-based surgical wound swabbing warrants urgent investigation as a strategy to improve timely diagnosis, optimise antibiotic prescribing, reduce AMR and enhance patient experience.

## Methods and analysis

### Study design

This is a multicentre, mixed-methods non-randomised feasibility study with the aim of evaluating the safety, acceptability and potential cost-effectiveness of patients self-swabbing surgical wounds at home. At hospital discharge, 40 adult patients across two hospital sites having had cardiac surgery will be given a self-swabbing kit and a set of instructions, coproduced by a patient and public involvement (PPI) group. All participants continue to receive usual postoperative follow-up and access to standard services as per site practice. Patients will be observed swabbing their surgical wounds at home by a researcher via Microsoft (MS) Teams and follow-up interviews will be conducted. Quantitative data will assess feasibility, safety, usability and clinical outcomes, while qualitative interviews with patients and staff stakeholders will explore acceptability and implementation.

An early health economic model will be developed alongside the clinical study to inform the wider research programme about the potential costs and impacts on antibiotic prescribing of introducing self-swabbing into the clinical pathway following cardiac surgery.

The study will run from January 2026 to May 2026, with participating sites open for recruitment from January to February. The protocol is reported using the Standard Protocol Items Recommendations for Interventional Trials 2025 checklist.^21^ The study flow chart is shown in figure 1.

**Figure 1 F1:**
[figure not shown]
Study flow diagram. GP, general practitioner.

### Study setting

The two cardiac centres chosen as research sites provide diversity in patient ethnicities, socioeconomic status and geographical location. Harefield Hospital (London Borough of Hillingdon) and the Royal Sussex County Hospital (coastal location) each perform approximately 1000 cardiac operations each year.^22^

### Study participants

Cardiac surgery was selected as the sample population as wound complications and infections are relatively common within this specialty and are among the most expensive to treat.^3^ A total of 40 adult patients (≥18 years) undergoing cardiac surgery via median sternotomy will be recruited: 25 from Harefield Hospital, Uxbridge and 15 from the Royal Sussex County Hospital, Brighton, UK. Additionally, patients who would like to take part in the study but require assistance can join along with an adult carer with the consent of both patient and carer. See onlinesupplemental materials 1  2 for participant and carer consent forms. Equipment (connected device and data allowance) will be provided for patients without internet access.

### Participant inclusion and exclusion criteria

Patients will be eligible to take part if they meet the following criteria:

Cardiac surgery ≥18 years old patients with a central chest wound, where the wound is a closed wound—assessed by the researcher.Patients having elective or urgent surgery.Patients who have been discharged home or to a care home.Willing and able to provide written informed consent prior to participation in the clinical investigation.Willing and able to comply with all study-related procedures, with digital resource/internet access.

Patients will be excluded for the following reasons:

Cardiac surgery patients with open wounds extending beyond skin level, or where deep tissue, organs or implants are visible, wounds with constant or heavy discharge of fluid, wounds leaking pus at the time of the video consultation.Patients with a dressing covering their wound at the time of the video consultation.Congenital or acquired immunodeficiency, bone marrow disease, diabetes, autoimmune conditions requiring immunosuppressive treatment, any immunosuppressive medication at the time of consent or within the last 4 weeks before consent due to potential issues with wound healing.Undergoing active cancer treatment at the time of consent or planning to start cancer treatment within the study period or completed cancer treatment within the last 4 weeks of the study commencing due to potential issues with wound healing.

### Sample size

As a feasibility study, no formal hypothesis testing is planned. Recruitment of 40 patients will allow estimation of a 90% successful self-swabbing rate with a 95% CI of 76% to 97%, calculated using the exact binomial method. A 90% success rate for self-swabbing was selected as the predefined ‘green-light’ criterion to justify progression to a full trial.

### Recruitment and consent

For planned cardiac surgery, potential participants on the elective surgical listing will be identified by the direct care team and will be told about the study at outpatients’ appointments.

For urgent cardiac surgery or transferred patients, potential participants on the urgent/transferred patient surgical listing will be identified by the direct care team and will be told about the study on the ward.

Potential participants will be identified by the direct care team and given a flyer containing brief information about the study. Verbal consent to share contact details with a member of the research team will be sought from patients who express an interest in taking part, which will be documented in the medical notes and on the screening log. Details of interested participants will be relayed to the researcher via email. Patients who express an interest in taking part will be telephoned by the researcher to discuss the study, answer any questions and will be sent a participant information sheet (PIS) via post or email, based on their preference. Individuals will be given a minimum of 24 hours to consider participation in the study.

Consent for collecting and use of wound culture samples will be obtained using the study informed consent form (ICF). Samples will not be stored for future research past the end of this study. This is stated in the ICF and PIS.

Each participant will be reimbursed £40 for their time plus £5 to cover internet costs. Participants can choose between cash paid into their bank account or an Amazon voucher.

### Withdrawal criteria

Participation in this study is voluntary. Patients are not required to participate and may decide to withdraw at any time. Participants may be discontinued from study participation on request, through non-compliance, through loss to follow-up, or if they are deemed ineligible after consent has been obtained.

Participants who no longer wish to participate can contact the researcher using the contact details provided in the PIS. Any data submitted prior to withdrawal will still be used in the study. Patients will no longer receive any contact from the research study, although they will continue to receive standard surgical care follow-up.

Study data already recorded in patient records for non-responding participants will be kept unless they explicitly withdraw their consent. Discontinued participants will be assessed for adverse events (AEs) at the final study-required contact (days 28–30) with continuing assessment of procedure-related AEs until these are resolved or stable (ie, unlikely to resolve or managed successfully with treatment). Attempts will be made to replace participants who withdraw post consent, are lost to follow-up or do not meet final eligibility criteria.

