## Outcomes

### Primary outcomes

Feasibility of home-based wound self-swabbing, defined as the proportion of patients completing the procedure successfully (ie, compliance with swabbing instructions) with samples received at the laboratory within 24 hours, and deemed suitable for processing.

Safety of the process, assessed through adherence to swabbing protocol, AEs and participant-reported concerns.

Acceptability of the swabbing process, assessed through Likert scale ratings and qualitative interviews.

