### Secondary outcomes

Acceptability of the swabbing instructions and kit, assessed through Likert scale ratings and qualitative interviews.Usability of swabs, including courier transport times and number of viable swabs for testing.New swabbing at home pathway, generated from stakeholder interviews and cost-effectiveness work.Recruitment and retention rates, adherence and completeness of data, including any barriers to participation and demographics.

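### Participants who withdraw or are lost are replaced, but nothing says that they stay in the denominator to which the 90% progression criterion applies

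*Protocol article*

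**What the plan says.** Four statements in the protocol article bear on this.

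- **Withdrawal criteria.** The replacement rule is: "Attempts will be made to replace participants who withdraw post consent, are lost to follow-up or do not meet final eligibility criteria". The same section lists the grounds for stopping participation: "Participants may be discontinued from study participation on request, through non-compliance, through loss to follow-up", with ineligibility discovered after consent as a fourth. It also keeps and uses data given before a withdrawal.
- **Primary outcomes.** Feasibility is "the proportion of patients completing the procedure successfully (ie, compliance with swabbing instructions) with samples received at the laboratory within 24 hours", with the further condition that the laboratory can process the sample. The text does not say whether the patients in this proportion are those consented, those given a kit or those who attempted a swab.
- **Sample size.** "Recruitment of 40 patients will allow estimation of a 90% successful self-swabbing rate with a 95% CI of 76% to 97" per cent, "calculated using the exact binomial method". Then: "A 90% success rate for self-swabbing was selected as the predefined ‘green-light’ criterion to justify progression to a full trial".
- **Secondary outcomes.** These include "Recruitment and retention rates, adherence and completeness of data, including any barriers to participation and demographics".

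Two other places give context. Study design says that 40 patients receive a kit at hospital discharge. Data analysis plans a CONSORT flow diagram and counts of missing data, and uses the success proportion to help size the full trial.

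**The concern.** Kits are handed over at discharge, and the observed swab takes place 1 to 21 days later. Someone who takes a kit home and then withdraws, cannot be reached or does not join the call has not completed self-swabbing at home. For a feasibility outcome that is a failure, and it is information the study is meant to produce.

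The only handling the article states for a participant who withdraws or is lost is an attempt at replacement. The total is given as 40 throughout, and the only precision figure is for 40. Recruiting substitutes until 40 remain, and then computing successes out of 40, follows naturally from those statements. On that reading, people who failed by leaving are exchanged for people who did not leave.

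The figure at stake decides whether a full trial follows and feeds its sample size. The direction of the effect is known: taking non-successes out of a denominator cannot lower a proportion.

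**Working it through.** **Inputs.** From the article: n = 40, target rate 90% (36 of 40), exact binomial 95% interval, criterion read as an observed rate of at least 90%. Assumed, because the article gives no figure: the number *w* of kit recipients who leave before a primary result and are replaced, the loss rate after receiving the kit, and the success rate among those who stay.

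**Step 1: the plan's own figure.** The exact (Clopper-Pearson) interval for 36/40 is 76.3% to 97.2%. This reproduces the stated 76% to 97%.

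**Step 2: the same 36 successes with replaced people kept in.** The rate is 36/(40 + *w*), each replaced person counting as a non-success.

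| *w* (assumed) | Rate | Exact 95% CI |
|---|---|---|
| 0 | 36/40 = 90.0% | 76.3 to 97.2 |
| 1 | 36/41 = 87.8% | 73.8 to 95.9 |
| 2 | 36/42 = 85.7% | 71.5 to 94.6 |
| 4 | 36/44 = 81.8% | 67.3 to 91.8 |
| 8 | 36/48 = 75.0% | 60.4 to 86.4 |

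One such person moves a result that just meets the criterion to below it.

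**Step 3: results above the threshold.** With *w* counted, meeting 90% needs at least 0.9 × (40 + *w*) successes. For *w* = 2 this is 37.8, so 38 of the final 40 must succeed (38/42 = 90.5%). For *w* = 4 it is 39.6, so all 40 must (40/44 = 90.9%). For *w* = 5 it is 40.5, which 40 people cannot supply (40/45 = 88.9%). How much replacement matters therefore depends on the margin above 36.

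**Step 4: chance of meeting the criterion.** Let *c* be the success rate among those who stay and *d* the loss rate after receiving the kit. Analysing 40 who stay gives P(X ≥ 36) with X ~ Bin(40, *c*). Counting all of 40 kit recipients gives the same tail with success rate *c*(1 − *d*).

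| *c* (assumed) | Final 40 after replacement | All 40 kit recipients, *d* = 5% | *d* = 10% | *d* = 20% |
|---|---|---|---|---|
| 0.90 | 0.63 | 0.29 | 0.10 | 0.01 |
| 0.92 | 0.79 | 0.42 | 0.16 | 0.01 |
| 0.95 | 0.95 | 0.65 | 0.29 | 0.02 |

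For example, *c* = 0.95 and *d* = 10% give a kit-level rate of 0.95 × 0.90 = 85.5%. The chance of meeting the criterion is then 0.95 under one denominator and 0.29 under the other. With no loss the two agree.

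**The case against.** The strongest reply is that replacement is a recruitment rule and does not define an analysis set. The article never says that a replaced person leaves a denominator. It refers to recruiting 40, says that 40 are given a kit at discharge, and keeps data collected before withdrawal. An analysis plan that is not shown may settle the matter. All of this is fair, and it is why the point is conditional. It does not dispose of it: the replacement rule and the progression threshold both stand in this document, and no sentence says how they fit together. Someone who leaves before swabbing has given no primary result to keep.

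It is also fair that not everyone replaced is a primary failure. A person lost after the laboratory has received the swab already has a primary result. A person who withdraws before discharge never had a kit. A person found ineligible at the wound check before swabbing is excluded by design. The figures above concern only kit recipients who leave before a primary result, and they overstate the effect if other replaced people are included in *w*.

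Two stronger readings are tempting and not supported.

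- A reader might infer that retention is biased too. Retention is a listed outcome and a flow diagram is planned, so it can be computed over everyone who consented. Its denominator is unstated, but no bias is shown.
- A reader might infer that non-compliant participants are swapped out, since non-compliance is a ground for discontinuation and compliance is part of the primary outcome. Non-compliance is not among the grounds for replacement.

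**Conclusion.** The point holds in a conditional form. The article states a replacement rule and a 90% threshold tied to 40 patients, and it leaves open whether replaced kit recipients count. If the final 40 are analysed, the reported rate is at least as high as the rate among everyone given a kit, and higher whenever one of them leaves before a primary result. A result exactly at the threshold is reversed by one such person (90.0% to 87.8%); four bring it to 81.8% (67.3 to 91.8).

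The direction follows from arithmetic alone. The size rests on assumed losses and success rates, for which the article gives no values. A reader might go further and conclude that the 40 analysed are those who reached the video call. The text permits that but does not say it, and the Study design statement that 40 patients are given a kit points the other way. Because this single proportion carries the progression decision, the denominator should be fixed before results are seen.

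**What to change.** In Sample size, Withdrawal criteria and Primary outcomes:

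1. State that replacing a participant does not change any denominator.
2. Define the primary proportion over all consented participants given a kit at discharge, and apply the 90% criterion to it.
3. Count as non-success any withdrawal, loss, missed call or absence of a received swab that occurs before a primary result exists. Someone lost after a primary result keeps that result.
4. Show those found ineligible at the pre-swab wound check separately, with a sensitivity analysis that includes them in the denominator.
5. Report the proportion among those who attempted swabbing as supplementary.
6. Compute retention over all who consented.

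No extra patients or new data collection are needed. Added interviews with people who never swabbed are not proposed, partly because the article ends study contact with those who withdraw. The cost is a less favourable stated rate and slightly more analysis. If replacements are recruited, the denominator will exceed 40 and the interval should be computed on the actual number.
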